## Abstract

**Background:**

Previous research suggests that self-management programs for people with chronic pain improve knowledge and self-efficacy but result in negligible effects on function. This study will investigate the effectiveness self-management support with pain science education and exercise on improving function for people with chronic pain in comparison to a wait-list control. A secondary objective is to determine which variables help to predict response to the intervention.

**Methods/Design:**

This study will be an unblinded, randomized controlled trial with 110 participants comparing a 6-week program that includes self-management support, pain science education and exercise to a wait-list control. The primary outcome will be function measured by the Short Musculoskeletal Function Assessment - Dysfunction Index. Secondary outcomes will include pain intensity measured by a numeric pain rating scale, pain interference measured by the eight-item PROMIS pain interference item-bank, how much patients are bothered by functional problems measured by the Short Musculoskeletal Function Assessment - Bother Index, catastrophic thinking measured by the Pain Catastrophizing Scale, fear of movement/re-injury measured by the 11-item Tampa Scale of Kinesiophobia, sense of perceived injustice measured by the Injustice Experience Questionnaire, self-efficacy measured by the Pain Self-Efficacy Questionnaire, pain sensitivity measured by pressure pain threshold and cold sensitivity testing, fatigue measured by a numeric fatigue rating scale, pain neurophysiology knowledge measured by the Neurophysiology of Pain Questionnaire, healthcare utilization measured by number of visits to a healthcare provider, and work status. Assessments will be completed at baseline, 7 and 18 weeks. After the 18-week assessment, the groups will crossover; however, we anticipate carry-over effects with the treatment. Therefore, data from after the crossover will be used to estimate within-group changes and to determine predictors of response that are not for direct between-group comparisons. Mixed effects modelling will be used to determine between-group differences for all primary and secondary outcomes. A series of multiple regression models will be used to determine predictors of treatment response.

**Discussion:**

This study has the potential to inform future self-management programming through evaluation of a self-management program that aims to improve function as the primary outcome.

**Trial registration:**

ClinicalTrials.gov NCT02422459, registered on 13 April 2015.

## Background

Approximately 19 to 29 % of Canadians, Americans and Europeans experience chronic pain [1–3], and pain-related disability is the largest contributor to years lived with disability [4]. Pain related-disability has an important impact on the quality of life, workplace productivity and the healthcare system [5–7]. It is important, therefore, to investigate strategies to improve quality of life and reduce pain-related disability for people living with chronic pain.

Self-management refers to an individual’s “ability to manage the symptoms, treatment, physical and psychosocial consequences and life style changes inherent in living with a chronic condition. Efficacious self-management encompasses ability to monitor one’s condition and to effect the cognitive, behavioural and emotional responses necessary to maintain a satisfactory quality of life.” [8] Self-management support aims to increase participants’ skills and confidence in managing their health through the provision of education and supportive interventions.

Self-management programs commonly evaluated in the literature have included education on a number of self-management strategies and often an opportunity to practice these skills: problem solving, communication with health care providers, use of healthcare resources including medication, general stretching, strengthening, and aerobic exercise, goal setting, diaries, self-monitoring, relaxation, symptom management strategies and cognitive strategies to help cope with pain [9, 10]. Evidence on the effectiveness of self-management support for people experiencing chronic pain is limited. Most research investigating the impact of self-management support on pain and disability include people with either arthritis or low back pain [9]. The evidence suggests self-management support improves knowledge and self-efficacy, but does not produce clinically important effects on pain or function [9–11]. It is not clear whether these results generalize to more diverse populations of people with chronic pain.

Two treatment approaches for people with chronic pain that have not been included in traditional self-management programs and demonstrate improvements in function are pain neurophysiology education and individualized, goal-oriented exercises. Pain neurophysiology education has been defined as an educational intervention and is useful for “describing the neurobiology and neurophysiology of pain, and pain processing by the nervous system” [12]. Pain neurophysiology education is effective for individuals with chronic low back pain [12–14], whiplash-associated disorder [15] and chronic fatigue syndrome [16]. The influence of pain neurophysiology education on pain and function in other chronic pain conditions has yet to be investigated with a rigorous trial. Similarly, while most self-management programs encourage participation in exercise and physical activity; most have not included individualized exercise programs despite evidence of reduced disability for both musculoskeletal and neuropathic pain conditions with these approaches [17–21]. The intervention evaluated in this study will be self-management support that incorporates individualized exercises and pain neurophysiology education with a primary aim of improving function.

It is also not clear from previous research which persons are most likely to respond to chronic pain self-management support. Previous research has suggested a number of factors that may contribute to chronic pain and reduced functional rehabilitation outcomes. For example, high initial pain levels [22–24], female sex [23], lower expectations of recovery [25], low pressure pain thresholds [26], cold hyperalgesia [27–29], catastrophic thinking [30–32], sense of perceived injustice [33] and fear of movement or re-injury [34–36] have all been associated with chronic pain, disability, or poor rehabilitation outcomes. Some of these variables have been suggested as prognostic indicators with more consistency than others. This study will investigate whether some of these prognostic indicators help predict response to chronic pain self-management support with pain education and individualized exercise.

### Objectives

#### Primary objective

This study will test the hypothesis that participants with chronic pain experience greater improvement in function over 18 weeks with 6 weeks of Chronic Pain Self-management Support with Pain Science Education and Exercise (COMMENCE) in comparison to a wait-list control.

#### Secondary objectives

This study will test the hypotheses that people with chronic pain experience greater pain intensity, pain interference, self-efficacy, catastrophic thinking, fear of movement/re-injury, pain neurophysiology knowledge, bother by difficulty with functional activities, fatigue, depressive symptoms, healthcare utilization and work status with COMMENCE in comparison to a wait-list control after 18 weeks.This study will compare the change in outcomes demonstrated by the wait-list group during their treatment period (18 to 36 weeks) to the change demonstrated during the wait-list period (0 to 18 weeks).This study will estimate whether the impact of the intervention is maintained over an intermediate follow-up term (18 to 36 weeks) in the treatment group.This study will determine whether the estimate of the magnitude of the effect is influenced by an 18-week delay.This study will identify demographic, psychological or psychophysical variables that are predictive of treatment response.

## Methods/Design

### Study design

This study is a randomized trial with two parallel groups. Participants will be allocated in a 1:1 ratio to treatment and wait-list groups. After the 18-week assessment (after the 6-week treatment period and the 12-week follow-up), the group initially receiving COMMENCE will receive no treatment, and the group initially on the wait-list will receive COMMENCE for 6 weeks. Both will be assessed again at 25 and 36 weeks from the baseline (1 and 12 weeks after the wait-list group finishes treatment) (See Fig. 1 for study flow). During the treatment, wait-list or follow-up periods, participants can continue with usual care with their family physician.

**Fig. 1 Fig1:**
[figure not shown]
Study flow diagram

Between-group comparisons (objectives 1 and 2) will be limited to the 0- to 18-week period prior to the wait-list group receiving treatment. However, an 18- to 36-week period was added for ethical reasons (that is, the wait-list group will receive the treatment) and to allow four additional analyses to address objectives 3 to 6.

### Blinding

Due to the nature of the treatment and comparison, participants and the treating physiotherapist will not be blinded to group allocation. The assessor who is completing the two objective measures will be blind to the treatment allocation at all assessment time points. The investigator performing the analysis will be blinded to the treatment allocation.

### Participants and setting

For the purposes of this study, 110 participants with chronic pain will be recruited at Woodstock and Area Community Health Centre (WACHC) in Woodstock, Ontario, Canada. All participants will be referred to the program by a healthcare provider at WACHC. WACHC has an interdisciplinary team of healthcare providers that work collaboratively to provide primary care, health promotion and community development programs to priority populations in Oxford County, Ontario, Canada. Since participants will be referred from WACHC, they will meet at least one of the criteria for WACHC’s priority populations: addictions concerns, mental health challenges, low incomes, lack of health insurance, or isolated seniors. Therefore, this sample will include people often excluded from research and treatment by barriers to accessing healthcare.

Included participants will all have been experiencing noncancer related chronic pain. Chronic pain will be defined as occurring in anyone who has been experiencing pain for greater than 12 weeks. The pain can fluctuate in intensity, but the patient must report experiencing pain on a daily basis over the 3-month period. The presentation can be that of musculoskeletal pain or neuropathic pain and can be associated with a traumatic (for example, injury or surgery) or nontraumatic etiology (for example, degenerative changes or pain of unknown etiology). Exclusion criteria will include cancer related pain, medical “red flags” suggestive of a non-neuromusculoskeletal etiology of symptoms, casted fracture or surgery within the last 26 weeks and evidence of upper motor neuron lesion. “Red flags” could include unremitting night pain, palpable tumor, sudden weight loss or weight gain, bowel or bladder incontinence, saddle anaesthesia, bilateral or multisegmental loss of sensory or motor function, fever/chills, diplopia, dysphagia, dysarthria, drop attacks, or nystagmus.

### Sample size

The sample size necessary for a randomized controlled trial with three repeated measures at 0, 7 and 18 weeks was calculated using online sample size software (GLIMMPSE 2.0) using methods detailed by Muller et al. [37–39]. The calculation was performed using a significance level of 0.05, a power of 0.8, a minimum detectable mean difference between groups of 10 points on the Short Musculoskeletal Function Assessment Dysfunction Index (SMFA-DI) [40] at both 7 weeks and 18 weeks, and a standard deviation at each time-point of 23 points on the SMFA-DI based on baseline data from a series of 20 people with chronic pain referred to physiotherapy at WACHC. The calculations were made assuming a correlation between baseline and 7 weeks of 0.84, a correlation between baseline and 12 weeks of 0.82, and a correlation between 7 weeks and 18 weeks of 0.84, based on the same clinical population. The needed sample size calculated was 88 participants. To account for a potential 20 % drop-out rate, the investigators will recruit 110 participants (n = 55 in each group).

### Allocation

The allocation sequence will be generated by a study investigator ([name]) who is not involved in the enrollment of participants or assigning interventions. A computer-generated blocked random number schedule will be used to determine allocation sequence. The block size will be unknown to the other study investigators. Participants will only be assessed and randomized if agreeable to participating in the group that starts one week after the assessment. If participants are unavailable for the upcoming group, both the assessment and randomization will be deferred. The allocation sequence will be concealed through the use of sequentially numbered, opaque envelopes, which will be opened by the physiotherapist (JM) and communicated to the patient after the initial assessment is completed.

### Enrollment

Patients will be screened and enrolled by the single treating physiotherapist (JM) after receiving a referral from a healthcare provider on the WACHC interdisciplinary team. The healthcare providers at WACHC will be instructed to refer anyone with noncancer related pain for at least 3 months. The physiotherapist will then screen to determine whether the participant meets the inclusion or exclusion criteria for participation in the trial.

### Intervention/treatment

COMMENCE consists of two visits with a physiotherapist per week over 6 weeks. One of the two visits is in a group setting, where the emphasis is on pain science education and self-management strategies using cognitive behavioral principles to support behavior change. The second visit is an individualized, one-to-one session focused on providing support to implement self-management strategies and develop an individualized, goal-oriented exercise program. Both the individual sessions and the group sessions will be carried out by a single physiotherapist (JM) for all participants.

#### Group pain neurophysiology and self-management education

The group sessions will include two to six people. The reason for a maximum of six people is pragmatic due to the maximum number of individual appointments the physiotherapist can accommodate in his schedule at the community health centre. The treatment group will proceed with as few as two people in case of low recruitment or high drop-out rate. The group sessions will be interactive 1.5 hour sessions once per week over 6 weeks. The participant will be educated on science of pain [12, 41] including the function of the nervous system, other systems involved in the pain experience, changes in these systems when pain persists, neuroplasticity, and self-management strategies to apply the information learned with the goal of increasing physical activity and participation in life role activities while controlling symptoms. The self-management strategies included in this study are informed by evidence as well as self-efficacy theory and social cognitive theory [42–45]. Self-management strategies will include progressive goal setting [46–48], activity scheduling [49, 50], thought monitoring [51], relaxation [52], sleep education [53], reflection [51], self-monitoring [10], graded activity [53–55] and exercise [19, 20]. The self-management education has been designed with the priority populations in mind. Lower average income is one of the priority populations, and this is associated with lower levels of education and literacy [56]. The material will be targeted toward those with less than a high school education. Participants will be given a workbook that guides them through the self-management strategies including goal setting, activity scheduling, using an activity and exercise log, thought monitoring and graded activity planning. It will be reviewed between the physiotherapist and participant at each individual session to facilitate communication, encourage discussion regarding an individual implementation plan for each of the self-management strategies discussed in the group, and to provide an opportunity to review any material covered in the group session.

#### Individualized self-management and exercise

The individualized sessions will be pragmatic 30 to 45 minute sessions once per week. The content will be tailored to the individual and delivered by the same physiotherapist (JM) who delivers the group sessions. The individualized sessions will include developing an implementation plan for the self-management strategies discussed in the group session. Participants will also collaborate with the physiotherapist on a graded activity plan to work towards functional goals and individual exercises to improve functional abilities to facilitate achieving functional goals. There will be three types of exercises encouraged. The first (i) is frequent pain-free movement, four to six times per day, six to ten repetitions at a time. Participants collaborate with the physiotherapist to find simple movements that can be performed easily throughout their daily routines. The purpose of these exercises is to reduce sensitivity to movement and build confidence with movement that does not increase pain. The second (ii) are exercises that simulate functional tasks needed to perform goals, one to two times per day at an intensity that allows the individual to perform eight to 15 repetitions at a time. The purpose of these exercises is to increase functional abilities needed to resume participation in life-role activities and participation goals set by the participant. Education regarding progression will be provided frequently throughout the program. The third (iii) is regular aerobic exercise. Participants will choose any aerobic activity they would like to participate in, set a baseline volume and intensity for that activity and create a plan with the physiotherapist for progression over time. The volume and intensity will be determined using recommendations that participants do not need to avoid pain at the time of exercise, but should choose an intensity that does not result in pain 1 to 2 hours after exercise. All three types of exercise will be delivered with messaging consistent with self-management education that suggests exercise is an effective way to manage pain and to prepare for increases in participation in physical activity and life-role activities.

#### Co-intervention

Participants will be free to continue with other treatments. Other treatments will be recorded through self-report at each assessment time-point and analyzed for between-group differences.

### Wait-list control

The wait-list control will be waiting to participate in COMMENCE after the 18-week assessment, and participants will be free to continue with “usual care.” This includes continued use of prescribed medications and recommendations from other healthcare providers. The wait-list comparison was chosen rather than a more robust comparator due to previous evidence, suggesting no difference in function when comparing other self-management programs to no-treatment or usual-care control groups.

### Withdrawing participants from this study

Participants may withdraw from the treatment at any time. Participants who choose to withdraw will be documented, and data will be analyzed as a member of the group to which they were randomly assigned.

### Ethical clearance

All participants will provide voluntary written informed consent after a discussion about what study participation entails and the potential benefits and risks. Informed consent will be obtained by the treating physiotherapist (JM) prior to the initial assessment after receiving a referral from a health care provider for each potential participant. Ethics approval has been obtained from Hamilton Integrated Research Ethics Board (HIREB #13-472).

### Outcomes

#### Self-report measures

All self-report measures have been demonstrated to be reliable and valid in a population of people with persistent pain. The ranges of each scale, as well as the minimal change considered clinically meaningful for this study, are described in Table 1.

**Table 1 Tab1:** Outcome measures and potential predictors of response

Construct	Outcome measure	Scale range	Minimal important difference
Function	Short Musculoskeletal Function Assessment - Dysfunction Index (SMFA-DI)	34–170	10 points^a^
How much participants are bothered by difficulty with functional activities	Short Musculoskeletal Function Assessment - Bother Index (SMFA-BI)	12–60	5.5 points^a^
Pain intensity	Numeric Pain Rating Scale (NPRS)	0–10	2 points [86]
Fatigue	Numeric Fatigue Rating Scale (NFRS)	0–10	1.4 points [87]
Pain interference	PROMIS Pain Interference Item Bank - 8 items	8–40	5 points^a^
Depressive symptoms	Patient Health Questionnaire - 9 (PHQ-9)	0–27	5 points [88]
Catastrophic thinking	Pain Catastrophizing Scale (PCS)	0–52	38 % of scale [89]
Fear of symptom exacerbation	11-item Tampa Scale of Kinesiophobia (TSK-11)	11–44	5.6 points [90]
Pain neurophysiology knowledge	Neurophysiology of pain test (NPT)	0–13	1.1 points^a^
Self efficacy	Pain Self Efficacy Questionnaire (PSEQ)	0–60	11 points [91]
Work status	Working versus not-working		
	Working full hours versus modified hours		
	Working full duties versus previous duties		
Healthcare utilization	# of health care visits during 12 weeks prior to treatment versus health care visits during 12-week follow-up period		
Post-traumatic stress symptoms	Post-traumatic Stress Disorder Checklist	17–85	
Sense of perceived injustice	Injustice Experience Questionnaire (IEQ)	0–48	
Medication use	Number of medications		
	Medication by class		
Comorbidities	Disease count		
Cold sensitivity	A novel test of cold sensitivity		
Pressure sensitivity	Pressure Pain Threshold (PPT)		

Legend: This table depicts each construct being measured as either an outcome or potential predictor of response, the measure used to evaluate that construct, the range of the scale (if applicable), and the minimal important difference for scales that will be measured as outcomes

^a^In the absence of an established MCID or MDC, change greater than half a standard deviation will be considered clinically meaningful [92]. In these instances, clinical data from Woodstock and Area Community Health Centre was used to establish the standard deviation

The primary outcome will be function as measured by the Short-Musculoskeletal Function Assessment - Dysfunction Index (SMFA-DI) [40].

Secondary outcomes will include the following:Short Musculoskeletal Function Assessment - Bother Index (SMFA-BI) [40]Numeric Pain Rating Scale (NPRS) [57]Numeric Fatigue Rating Scale (NFRS) [58]PROMIS Pain Interference Item Bank - 8 items [59]Patient Health Questionnaire (PHQ-9) [60–62]Pain Catastrophizing Scale (PCS) [30, 63, 64]Tampa Scale of Kinesiophobia - 11 (TSK-11) [65]Pain Self Efficacy Questionnaire (PSEQ) [66–68]Neurophysiology of Pain Questionnaire (NPQ) [69]number of health care visitswork status

Potential predictors of response will include baseline measures for each of the outcome measures listed above as well as:Post-traumatic Stress Disorder Checklist (PTSD-C) [70, 71]Injustice Experience Questionnaire (IEQ) [33]number of medications [72]disease count [72]

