### Analysis

Statistical analysis will be conducted using Stata software, version 13 (StataCorp, College Station, TX, USA). Baseline characteristics for both treatment and wait-list groups will be presented as means and standard deviations for normal data, and medians and interquartile range for non-normal data, and number of patients and percentages for categorical data. Between-group comparisons will be made for baseline data using a Student’s *t*-test for continuous data and Chi squared or Fisher’s exact test for categorical variables to determine the results of the randomized allocation.

To address objectives #1 and 2, between-group differences in change in primary (SMFA-DI) and secondary outcomes will be analyzed using linear mixed-effects modelling with repeated measures at 0, 7, and 18 weeks. A *P* value of less than 0.05 will be considered indicative of statistical significance for all comparisons. The minimum changes required for the change to be considered clinically meaningful for each scale are listed in Table 1. An advantage of using linear mixed-effects modelling is the ability to utilize all available data points without multiple imputation when there are multiple missing data points [75]. Between-group comparisons will be limited to data collected before the 18-week assessment time point due to anticipated carry over effects due to the long-term changes in function associated with exercise approaches for people with chronic pain [19, 20]. Analysis will use intention-to-treat principles.

To address objective #3, a within-group analysis in the wait-list group will be performed comparing the change in function during the treatment period (weeks 18 to 36) to the change in function during the wait-list period (weeks 0 to 18) using a mixed effects model. If there is no change during the wait-list period, this analysis allows for a secondary estimate of treatment effect similar to a diamond response design [76]. Goldsmith et al. suggest that if the magnitude of the effect of the intervention is similar to that estimated through the comparison between groups during the 0 to 7 week period, then they may be pooled for a more precise estimate of treatment effect [76].

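### Table 1 sets the Pain Catastrophizing Scale threshold at 38% of the scale, or 19.76 of 52 points, a bar so high that a substantial benefit would be labelled not clinically meaningful

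*Protocol article*

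**What the plan says.** The Self-report measures section of the protocol article introduces the threshold column by saying that the ranges, and "the minimal change considered clinically meaningful for this study, are described in Table 1". The row for catastrophic thinking reads "Pain Catastrophizing Scale (PCS) 0–52 38 % of scale [89". The other nine scales with a threshold all have one in points.

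The Analysis section brings the column into the between-group comparisons for objectives 1 and 2: "The minimum changes required for the change to be considered clinically meaningful for each scale are listed in Table 1". Statistical significance is a separate criterion: a P "value of less than 0.05 will be considered indicative of statistical significance for all comparisons".

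Footnote a to Table 1 supplies a fallback for scales without an established value: "change greater than half a standard deviation will be considered clinically meaningful". The catastrophizing row does not carry that footnote; it cites a source.

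Eligibility, under Participants and setting, rests on pain and its duration: "Chronic pain will be defined as occurring in anyone who has been experiencing pain for greater than 12 weeks". No minimum catastrophizing score is required at entry.

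**The concern.** A threshold for clinical meaningfulness has to be a change that the scale can show and that a plausible benefit can reach. A percentage needs a base. Here the stated base is the scale itself, with its 0–52 range printed alongside, and this gives a value of a different order from every other row. Nowhere does the article restate the threshold in points or as a share of baseline.

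At stake is how the result on catastrophic thinking, a named secondary outcome, is interpreted. If the entry is followed literally, a clear and sizeable reduction would be reported as falling short of clinical meaning. If the entry is reinterpreted once results are known, the threshold becomes a post hoc choice.

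**Working it through.** **Inputs.** From Table 1: the range and threshold of each scale. From Analysis: the quantity judged is the between-group difference in change over 0, 7 and 18 weeks. Assumed, because the article gives no figure: a baseline mean on the Pain Catastrophizing Scale (PCS) of 20 to 30, and no mean change on the wait-list. The 38% comes from a cited source, so there is no figure in the article to reproduce.

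**Step 1: the threshold in points.** 0.38 × (52 − 0) = 19.76 points.

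**Step 2: comparison with the other rows.** Threshold divided by (maximum − minimum):

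| Scale | Calculation | Share of range |
|---|---|---|
| SMFA-DI | 10/136 | 7.4% |
| NPT | 1.1/13 | 8.5% |
| SMFA-BI | 5.5/48 | 11.5% |
| NFRS | 1.4/10 | 14.0% |
| PROMIS pain interference | 5/32 | 15.6% |
| TSK-11 | 5.6/33 | 17.0% |
| PSEQ | 11/60 | 18.3% |
| PHQ-9 | 5/27 | 18.5% |
| NPRS | 2/10 | 20.0% |
| PCS | 19.76/52 | 38.0% |

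The PCS share is 38/20 = 1.9 times the next largest.

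**Step 3: the floor.** The largest possible fall equals the starting score. In whole points, a score of 19 or less cannot fall by 19.76.

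**Step 4: the bar for a group mean.** With no wait-list change, the treated mean must itself fall by 19.76 points. The proportional fall is 19.76 divided by the baseline mean:

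- mean 20: 19.76/20 = 98.8%, leaving a mean of 0.24
- mean 25: 19.76/25 = 79.0%, leaving 5.24
- mean 30: 19.76/30 = 65.9%, leaving 10.24

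If the wait-list mean improved, the treated mean would have to fall further still; if it worsened, less far.

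**Step 5: how much the base matters.** If the entry meant 38% of the baseline score, which the article does not say, the threshold would be 0.38 × 20 = 7.6 points, 0.38 × 30 = 11.4 or 0.38 × 40 = 15.2. The two readings coincide only at a baseline of 52.

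**The case against.** The strongest reply is that the value is cited, that the source cannot be seen here, and that the threshold touches nothing inferential. Most of this stands. Objective 2 is tested by the mixed model at P < 0.05, and PCS is one of eleven listed secondary outcomes. A citation does not remove the difficulty, though: if the source did mean 38% of the range, the floor and the size of the required mean fall remain.

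Four stronger readings are tempting, and the documents do not support them.

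- A reader might infer that a large share of participants will be counted as non-responders because of the floor. The article plans no responder analysis. It plans a comparison of mean change, and any such share would rest on an assumed PCS distribution.
- A reader might infer that the entry is disproved by the half-SD rule, since no SD possible on this scale would yield 19.76. That rule applies only where no established value exists; the PCS row cites a source and is not governed by it.
- A reader might infer that percent of baseline was plainly intended. The text says the opposite, and the intended meaning cannot be settled without the source.
- A reader might infer that the finding on catastrophizing is decided in advance. The estimate, its confidence interval and the P value are untouched; only the clinical label is affected.

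**Conclusion.** The concern holds in a limited form. The entry fixes a threshold of 19.76 points, which is out of line with the other nine scales (7.4% to 20% of range), cannot be reached from a score below 20, and is corrected nowhere in the article. These statements follow from Table 1 alone.

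The 66% to 99% average fall rests on the assumed baseline mean of 20 to 30 and a flat wait-list. A higher baseline mean would lower it, to 49% at a mean of 40 (19.76/40).

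The consequence is that a substantial benefit on catastrophizing would be described as not clinically meaningful. It is worth correcting because this is a stated decision rule with an unusable base, rather than detail left for an analysis plan. The primary SMFA-DI analysis and the sample size of 110 do not depend on it.

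**What to change.** Before the analysing investigator's blind is lifted and before PCS results are compared by group, check the entry against its cited source and replace the percentage of the scale with a threshold whose base is stated and usable.

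- If the source supports percent change from the participant's own baseline, say so in Table 1. Give the equivalent in points at the observed mean baseline, and judge the between-group difference against that value.
- If the source supports no usable value, treat the PCS as having no established threshold and apply the half-SD rule of footnote a, in points. Use clinic PCS data if they exist (the article shows none for this scale); otherwise use the trial's baseline SD pooled over both groups, which needs no knowledge of allocation.

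The cost is one table entry and a check of one source, with no new data or participants. The drawback of a percent-of-baseline rule is that it is undefined at a baseline of zero and easily met at very low baselines; the half-SD rule avoids both.
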